### Study Population

Women and men diagnosed with CAD will be included in the study. The following eligibility criteria have been defined:

Inclusion criteria: (1) aged ≥18 years (there is no a priori upper age limit); (2) documented stable CAD and referred for CR (at >2 weeks but <10 weeks after percutaneous coronary intervention or >4 weeks but <12 weeks after coronary artery bypass grafting or myocardial infarction: with or without ST-segment elevation), or having documented CAD by coronary angiography (stenosis in a major coronary artery >50%); (3) access and ability to operate a smartphone; and (4) proficiency in the native language of the country (ie, German, Spanish, and Dutch).Exclusion criteria: (1) unable to fully understand the provided study information and consequences of participating in the study; (2) presence of an impairment interfering with the use of the app or devices (eg, blindness and wheelchair bound); (3) known diagnosis of an active malignant tumor (cancer) or any other medical condition associated with a life expectancy of <1 year; (4) cardiovascular, cerebrovascular, or other unstable medical condition; (5) having a pacemaker or life vest; and (6) refusal to provide informed consent. If any of the exclusion criteria emerge during the 1-year duration of the project, participants will be withdrawn from the study.

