### Randomization and Blinding

Participants will be randomly assigned (1:1) to either the intervention group or the care-as-usual group. A computer-generated randomization sequence will be delivered, in an Excel (Microsoft Corp) file, to each recruitment site and will be concealed by one of the researchers by covering the allocation numbers with “black paint.” Randomization will be conducted and dated, per patient, by the researcher after the participant has signed the informed consent and baseline assessments have been performed.

Given the nature of the study, blinding of the researchers or participants during the behavioral intervention trial is not possible. However, the analysis of blood samples and all other outcome measures will be conducted by research team members who are blinded to the participants’ group assignment.

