#### Monitoring of Physical Activity, Hemodynamics, and Electrocardiogram During Daily Life Activities

All patients randomly assigned to the intervention group will be equipped with an activity tracker (Vivosmart 4, Garmin), an upper-arm BP monitor (Tel-O-Graph BT, IEM), and a 3-channel Holter monitor (netECG, livetec). Data from the activity tracker will be collected via Bluetooth on the patients’ smartphone and transmitted directly to the TIMELY-Net server (Semdatex) using an application programming interface provided by FitRockr to comply with European data protection regulations. The BP monitor will be placed in the patient’s home, together with a data transmission hub (eConnect, IEM), which allows secured mobile transmission of data (GSM standard) via the IEM gateway to the TIMELY-Net server. Collected data are then displayed in the TIMELY dashboard for case managers and made available to patients via the TIMELY app on their mobile phones, which can be downloaded from the app store for Android and iOS devices (see below for a detailed description of the TIMELY app).

Electrocardiogram (ECG) monitor data will be analyzed retrospectively after the trial. In brief, data will be downloaded from the ECG device at each participating center and uploaded to the TIMELY platform. The data will then be analyzed by ECG specialists at the participating partner institution, TU Dresden, using deep learning technology as described elsewhere [42]. Clinicians at the 3 centers will be involved to verify incidental findings of ECG abnormalities.

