### Statistical Analysis

For descriptive statistics, categorical variables will be compared with the *χ*^2^ test (Fisher exact test when appropriate). Continuous variables will be compared using independent sample *t* test or a nonparametric test where appropriate.

To address the main hypothesis, repeated measures ANOVA using generalized linear mixed modeling analysis will be used to investigate the effect of the intervention on changes from baseline to 6 months for the 2 primary end points (Coropredict score and a 6-minute walk test) using a 2 (intervention vs control)×2 (baseline to 6 months) design, accounting for potential baseline differences and correlations between baseline and 6 months assessments. Data for the primary outcomes will be analyzed according to the intention-to-treat principle.

For the secondary outcome measures, a similar approach will be used. To explore long-term effects at 12 months, 2 (group)×3 (repeated measure) mixed models will be used. In addition, univariable and multivariable regression analyses (both linear and logistic regression) will be used to examine cross-sectional and longitudinal associations between variables, with the type of regression analysis depending on the distribution characteristics of the variables.

Exploratory analyses will also include completer analyses and evaluation of trial adherence as related to the outcome measures. As this study includes multiple secondary outcome measures without correction for statistical type 1 error, the obtained results will be interpreted with caution and will primarily provide estimates of effect sizes related to the TIMELY intervention. Data will be analyzed using SPSS statistics (IBM Corp) [48] or equivalent.

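### Randomized patients who develop an exclusion criterion are withdrawn from the study, which conflicts with the intention-to-treat analysis and makes primary outcomes informatively missing before month 6

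*Protocol article*

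**What the plan says.** Under Study Population, after the eligibility lists, the protocol article says: "If any of the exclusion criteria emerge during the 1-year duration of the project, participants will be withdrawn from the study". Criteria 4 and 5 on that list read "4) cardiovascular, cerebrovascular, or other unstable medical condition; (5) having a pacemaker or life vest". Criterion 3 covers "known diagnosis of an active malignant tumor (cancer) or any other medical condition associated with a life expectancy of <1 year". Criterion 2 is an impairment that interferes with using the app or devices, with blindness and wheelchair use as examples.

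Under Randomization and Blinding: "Randomization will be conducted and dated, per patient, by the researcher after the participant has signed the informed consent", and after the baseline assessments. The withdrawal rule therefore acts on patients who already belong to an arm.

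Under Statistical Analysis: "Data for the primary outcomes will be analyzed according to the intention-to-treat principle". The primary model compares the arms "using a 2 (intervention vs control)×2 (baseline to 6 months) design". Analyses of completers are listed separately, as exploratory: "Exploratory analyses will also include completer analyses and evaluation of trial adherence as related to the outcome measures".

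**The concern.** Eligibility is a fact about a patient at entry. Once patients are randomized, cardiovascular instability, a new pacemaker or the loss of walking ability is something that happens during the trial, and it bears on what the trial measures. The CoroPredict score contains NT-proBNP and high-sensitivity troponin I, and the other primary outcome is walking distance. The rule removes such patients from the study and does not say that they are still assessed at 6 or 12 months.

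At stake is whether the primary comparison describes everyone randomized or only those who stayed stable. If withdrawal also differs between arms, the comparison itself is biased.

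**Working it through.** **The passages side by side**

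1. Who is affected: randomized patients in either arm, at any time in the year.
2. What they leave: the study. The rule is not limited to the intervention.
3. What the analysis needs: under intention-to-treat, a 6-month risk score and walk distance from everyone randomized, as far as obtainable.
4. Result: a patient withdrawn before month 6 has no primary outcome, by instruction of the protocol. A patient withdrawn after month 6 already has it, and only the 12-month analyses are affected.

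**Could withdrawal differ by arm?** Three features of the article make it plausible:
- Researchers and participants are not blinded during the trial.
- Only the intervention arm has home blood pressure transmission, dashboard tasks triggered by blood pressure deviations or reported symptoms, and regular case-manager contact. On devices: "All patients randomly assigned to the intervention group will be equipped with an activity tracker", together with a blood pressure monitor and a Holter recorder.
- Criterion 2 is worded around an app and devices that controls do not receive.

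**Size.** The article ties no figure to the rule, so there is nothing to reproduce. The values below are assumptions.

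Let w be the share of an arm withdrawn before month 6, and D the amount, in SD units, by which the withdrawn patients' 6-month outcome is worse than the analysis assumes for them (for a mixed model, worse than their baseline value predicts). Each arm's mean is then too favorable by w × D. With a common D:

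observed contrast − contrast in all randomized = D × (w_intervention − w_control)

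A positive value means that benefit is overstated.

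| Intervention | Control | D = 0.5 | D = 1.0 |
|---|---|---|---|
| 10% | 5% | 0.05 × 0.5 = +0.025 | 0.05 × 1.0 = +0.05 |
| 15% | 5% | 0.10 × 0.5 = +0.05 | 0.10 × 1.0 = +0.10 |
| 5% | 10% | −0.025 | −0.05 |
| 5% | 15% | −0.05 | −0.10 |
| 5% | 5% | 0 | 0 |

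**Benchmark.** With 180 per arm, two-sided alpha 0.025, power 0.80 and a correlation of 0.3 (all from Sample Size), the detectable difference in change is (2.241 + 0.842) × √(2/180) × √(2 × (1 − 0.3)) = 3.083 × 0.1054 × 1.183 ≈ 0.385 SD. The shifts are 0.025/0.385 ≈ 6.5% to 0.10/0.385 ≈ 26% of it.

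**Power is not the problem.** The article states f² = 0.15. Even on the more demanding reading f = 0.15, power at alpha 0.025 is 0.995 with 360 patients and 0.979 with 288 (20% lost).

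**The case against.** **The analysis may still be intention-to-treat in form.** Deletion of data is stated only for participants who opt out (Ethical Considerations), not for withdrawal under this rule. A mixed model can keep a withdrawn patient's baseline value in the assigned arm. This stands, so the documents do not support saying that these patients are discarded or that the analysis simply stops being intention-to-treat. It helps little, however. A patient with a baseline value only adds almost nothing on change. At the plan's own correlation of 0.3, baseline explains 0.3² = 9% of the variance at 6 months. Missing-at-random is doubtful when deterioration causes the missingness.

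**The direction is unknown.** A reader might infer that closer surveillance removes more sick patients from the intervention arm and so flatters the app. The article does not support that. If the intervention prevents deterioration, more controls are withdrawn and real benefit is hidden.

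**The difference in detection is smaller than it looks.** Holter data are analyzed only after the trial, so they are not a live trigger. The monthly calls are described as technical support and engagement. Serious adverse events are sought in both arms from patient reports and records. All this stands. What remains is the blood pressure and symptom alerts, the contact itself, and the wording of criterion 2.

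**Not every trigger is cardiac.** Active cancer is not a consequence of coronary disease. The point rests on the triggers that are related to the outcomes.

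**The Results say that everyone has completed 6 months.** Read literally, this confines the harm to the 12-month analyses. It may equally mean that the 6-month window has closed for all. Withdrawal counts would settle it.

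**Missing-data methods belong in the analysis plan.** They do, but this is a stated rule about who stays in the study. No analysis plan can recover blood samples and walk tests that were never taken.

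**Conclusion.** The point holds. The withdrawal rule and the intention-to-treat statement are both explicit, and they must be reconciled. Patients withdrawn before month 6 have primary outcomes missing for reasons related to those outcomes.

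Under the assumed rates and shortfalls, the shift in the contrast is 0.025 to 0.10 SD in either direction. It is zero when rates and shortfall are equal, but the result then still describes only patients who remained stable. Actual withdrawals, which the article does not report, could put the shift anywhere in that range or outside it.

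The article does not establish a bias toward benefit, nor that every withdrawn patient lacks a primary outcome. It also does not say whether safety monitoring stops at withdrawal.

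**What to change.** 1. State that an exclusion criterion emerging after randomization does not end follow-up or remove the patient from the analysis. Such patients are invited to all remaining assessments that they are able and willing to do, and are analyzed as randomized.
2. Report withdrawals under this rule by arm, reason and date, separating those before and after the 6-month assessment.
3. For both primary outcomes, add a sensitivity analysis for informative missingness, such as delta-adjusted or worse-than-average imputation, with the adjustment allowed to differ by arm.

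Whether and when a patient stops the intervention is a separate decision for the sponsor and clinicians; no rule on it is proposed here.

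The cost is a small amendment, a few extra follow-up contacts and a little more analysis. Inviting back patients already withdrawn may need ethics approval and renewed consent. At the article's date the 12-month follow-up was still open, so item 1 could still help there. Primary-outcome data missed at 6 months cannot be recovered, and for those patients items 2 and 3 are the remedy.

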### Sample Size

A total of 360 patients will be enrolled across 3 participating centers: Hospital Universitario de Santiago de Compostela, Spain (120/360, 33.3%); Clinic Königsfeld of the German Pension Fund at the University of Witten/Herdecke, Ennepetal, Germany (120/360, 33.3%); and Elisabeth-TweeSteden Hospital, Tilburg, the Netherlands (120/360, 33.3%). At each center, patients will be randomly assigned, with 60 (50%) out of 120 receiving the intervention in addition to care as usual, and 60 (50%) receiving care as usual. Of 360 patients, 180 (50%) will receive the intervention, and 180 (50%) patients will receive care as usual.

On the basis of participation rates in previous randomized controlled trials [33], it is expected that approximately 33% of patients will decline participation. It is expected that a total of 480 patients will have to be approached to include 360 participants across the 3 study sites. Sample size calculations were based on medium-large effect sizes and statistical power analyses were conducted using G*Power (version 3.1.9.4; Heinrich-Heine-Universität Düsseldorf) [34]. A sample of 120 patients per center will enable detection of a medium effect size. The *f*^2^ for the between-within group interaction is 0.15 in a mixed model ANOVA, with a power of 0.80 and a two-sided α level of 0.025 (0.05/2, as two primary outcomes will be evaluated; details are provided in the *Study Objective* section). In brief, the set of variables for this analysis was based on a 2 (between-group: intervention vs control)×2 (repeated measures at baseline and 6 months) mixed model ANOVA, assuming sphericity and a correlation of 0.3 between the repeated measures.

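### Sample Size: the stated power of 0.80 is not the power of the stated 2×2 design with 120 patients, and 480 approached does not fit a 33% refusal rate

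*Protocol article*

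**What the plan says.** The Sample Size section sets enrolment at 360, with 120 in each of three centers randomized 60 to 60. The power statement is made for one center: "A sample of 120 patients per center will enable detection of a medium effect size". The effect is printed as an f² which "for the between-within group interaction is 0.15 in a mixed model ANOVA, with a power of 0.80 and a two-sided α level of 0.025". That alpha is 0.05 halved, because the trial has two primary end points. The model has two groups and two time points (baseline and 6 months), "assuming sphericity and a correlation of 0.3 between the repeated measures". The software named is G*Power. One sentence earlier the effect is called medium-large; here it is medium.

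The Statistical Analysis section plans, for each of the two primary end points, one intention-to-treat comparison in a "2 (intervention vs control)×2 (baseline to 6 months) design". It names no analysis by center.

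On recruitment, the Sample Size section expects roughly 33% of patients to decline, and then says: "It is expected that a total of 480 patients will have to be approached to include 360 participants across the 3 study sites".

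**The concern.** Design, number of measurements, correlation, alpha, sample size, effect and power are all printed, so the 0.80 can be checked without outside information. It should come back from the other inputs, and it does not. Under one reading of the effect symbol the power is far higher, and under the other it is clearly lower.

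Readers use the power statement to judge what a null result rules out. Here the effect could be a difference in change of 1.55 SD (0.15 as f²) or 0.60 SD (0.15 as f), and neither describes the sensitivity of the planned comparison in all patients. The recruitment sentence has a separate arithmetic slip that any reader can verify.

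**Working it through.** **Inputs (Sample Size section).** k=2 groups, m=2 measurements, correlation ρ=0.3, sphericity (ε=1), two-sided α=0.025, N=120, effect 0.15 printed as f², power 0.80.

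**Formula.** For the within-between interaction, with f² defined on the SD of a single measurement, the noncentral F has
- λ = f²·N·m·ε/(1−ρ)
- df1 = (k−1)(m−1), df2 = (N−k)(m−1)

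In a 2×2 layout, a between-group difference in change D (in SD of one measurement) gives f = D/4, so D = 4f.

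**Attempt to reproduce 0.80 (df 1 and 118, critical F 5.155 at α=0.025).**

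| Reading | D | λ | Power, N=120 | N for 0.80 |
|---|---|---|---|---|
| f²=0.15 as printed (f=√0.15=0.387) | 1.55 SD | 0.15×120×2/0.7 = 51.43 | >0.999 | 26 |
| f=0.15 (f²=0.0225) | 0.60 SD | 0.0225×120×2/0.7 = 7.71 | 0.694 | 152 |

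A simulation with 20,000 replicates agreed: 1.000 for the first row and 0.699 for the second. Effect-size conventions that leave out the correlation do not rescue the figure: about 0.97 for f²=0.15 and 0.26 to 0.27 for f=0.15. With f=0.25 and the main formula, power is 0.990.

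**What comes close to 0.80.** Both candidates take 0.15 as f and change one further stated input.
- Three measurements, α=0.025: λ = 0.0225×120×3/0.7 = 11.57, df 2 and 236, power 0.796; 122 patients reach 0.80. The protocol does measure the outcomes at baseline, 6 and 12 months, and uses 2×3 models for long-term effects.
- Two measurements, α=0.05: λ = 7.71, power 0.787; 126 patients reach 0.80.

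**Detectable effect at 80% power, 2×2, ρ=0.3, α=0.025.**

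| N | f | f² | D = 4f |
|---|---|---|---|
| 120 (one center) | 0.168 | 0.028 | 0.67 SD |
| 360 (planned total) | 0.0965 | 0.0093 | 0.39 SD |
| 358 (randomized) | 0.0967 | 0.0094 | 0.39 SD |

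The protocol article gives no attrition rate. If 10% to 15% were missing (an assumption; N=324 to 306), f would be 0.102 to 0.105, or 0.41 to 0.42 SD. With all 360 and f=0.15, λ = 0.0225×360×2/0.7 = 23.14 and power is 0.995.

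**Patients to approach.** 360/480 = 0.75, so 480 implies 25% refusal. At 33% refusal, 360/0.67 = 537; at one third, 360/(2/3) = 540. Conversely, 480×0.67 = 322 enrolled.

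**The case against.** Several points can be made for the plan, and most limit the finding.

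- *As printed, the claim errs on the safe side.* With f²=0.15, 120 patients have at least 0.80 power. This stands: 0.80 fails as the power of the stated design, but a shortfall appears only if 0.15 is read as f, which the text does not print. It would be too strong to say that the statement overclaims on every reading.
- *A reader might infer that the alpha split was announced but not applied,* because f=0.15 at alpha 0.05 gives 0.787. The document does not support this. Three measurements at the stated alpha of 0.025 give 0.796, which is closer, and the software output is not shown.
- *A reader might infer an underpowered trial.* The pooled figures rule that out for an effect of f=0.15: power is 0.995 with 360, and 0.985 even with 306.
- *Sizing by center is a conservative choice, not an error,* and a condensed article may leave the pooled detectable effect and a dropout rate to the full protocol. This stands. The Limitations section says only that device burden might perhaps lead to early termination; it sets no expected rate.
- *The approach forecast has been overtaken:* the Results section reports 809 approached, and recruitment is closed. That lowers the stakes but does not make 480 agree with 33%.

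What remains is that the printed inputs contradict the printed power, and changing f² to f alone does not repair the sentence, because power then becomes 0.69.

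**Conclusion.** The concern holds as a reporting error. For the stated 2×2 design with ρ=0.3, two-sided alpha 0.025 and 120 patients, power is above 0.999 with f²=0.15 and 0.69 with f=0.15. Neither is 0.80, and the document does not allow the source of the mismatch to be determined. The refusal rate and approach target also disagree, by 57 to 60 patients.

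The result rests on the usual within-between formula with the correlation entered, which fits the inputs the section lists. No decision rule, analysis or enrolment number depends on the correction. Its value is that readers of the results can see what the trial could detect: about 0.39 SD for the pooled comparison if all 360 are analyzed and ρ=0.3 holds.

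**What to change.** Rewrite the power sentence, and carry the corrected version into the results report:

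1. State whether 0.15 is f or f², and how many measurements the calculation used.
2. Make power, effect and sample size agree at alpha 0.025. If the per-center statement is kept for the 2×2 design, 80% power with 120 patients is at about f=0.168 (0.67 SD difference in change).
3. Add the planned pooled analysis, for example: with 360 patients, a correlation of 0.3 and alpha 0.025 for each primary outcome, power is 0.80 at f=0.097, about 0.39 SD difference in change. Label any attrition-adjusted figure as an assumption.
4. Use one description of the effect, medium or medium-large.
5. Reconcile the recruitment forecast: either about 537 to 540 approached at 33% refusal, or 25% refusal with 480.

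The cost is wording only, with no extra patients and no change to the analysis. If 0.15 was meant as f, the per-center claim becomes less favorable; the pooled sensitivity is better than either reading of the present text suggests.

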#### Primary Objectives

The primary objective of the TIMELY study is to investigate whether the TIMELY intervention is superior to usual care in terms of the following:

Reducing the risk of 10-year mortality assessed by a validated biomarker risk score (CoroPredict, primary biomedical outcome) from baseline to 6 months. The Coropredict score assesses cardiovascular risk using a combination of laboratory-based parameters (including hemoglobin A_1c_, N-terminal pro-B-type natriuretic peptide, high-sensitivity troponin I, cystatin C, and high-sensitivity C-reactive protein) and demographic information (age, sex, and smoking status) [35].Increasing the 6-minute walking test distance (primary behavioral outcome indicating functional fitness level) from baseline to 6 months.

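### The 0.05/2 split for the two primary outcomes is valid, but Holm is never less powerful at the same family-wise error and could be specified at little cost

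*Protocol article*

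**What the plan says.** - **Sample Size.** The calculation is made "with a power of 0.80 and a two-sided α level of 0.025", and the level is explained as "0.05/2, as two primary outcomes will be evaluated". The f² "for the between-within group interaction is 0.15 in a mixed model ANOVA", "assuming sphericity and a correlation of 0.3 between the repeated measures". The power statement is attached to the single center: "A sample of 120 patients per center will enable detection of a medium effect size". The trial as a whole is three times that size: "A total of 360 patients will be enrolled across 3 participating centers".
- **Primary Objectives.** "The primary objective of the TIMELY study is to investigate whether the TIMELY intervention is superior to usual care" on CoroPredict and on 6-minute walk distance. The two are listed without ranking, and nothing says whether success needs one or both.
- **Statistical Analysis.** A group-by-time mixed model is named for both primary end points, with the analysis set given as "Data for the primary outcomes will be analyzed according to the intention-to-treat principle". No testing threshold or step-down rule is given for them. Type 1 error is mentioned only for the secondary outcomes, which are left uncorrected.
- **Results.** 358 patients were randomized, 6-month follow-up was complete as of January 2025, and results were expected in September 2025.

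**The concern.** Read as the decision rule, the fixed split calls an outcome negative whenever its p-value lies between 0.025 and 0.05, however clear the result on the other primary outcome. A walk-distance p-value of 0.03 would count as a failure even beside a CoroPredict p-value below 0.001. Holm would declare both, with the same 5% guarantee and with no extra patients, ranking or assumption.

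The Introduction (TIMELY subsection) hypothesizes both a lower risk and better fitness, so the chance of confirming both is relevant to the trial's own question. Recruitment is closed, so the testing rule is one of the few remaining ways to affect power.

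**Working it through.** **1. The plan's own figures.** 0.05/2 = 0.025. The two levels sum to 0.05, and for independent tests the family-wise error is 1 − 0.975² = 0.0494. The split controls error as intended.

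The 120 per center does not reproduce from its stated inputs. With G*Power's default noncentrality, λ = f²·N·m/(1 − ρ), m = 2 and ρ = 0.3:
- f² = 0.15, N = 120: λ = 0.15·120·2/0.7 = 51.4 and power is about 1.00. 80% power needs only N = 26. With the other noncentrality conventions it needs 66 to 68, and power at 120 is about 0.97.
- If 0.15 was meant as f: power at 120 is 0.69, and 80% needs N = 152.

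This is a separate matter. The comparison below is anchored on the stated 80% power per test, so it does not depend on how N was obtained.

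**2. Holm against the split at the stated power, correlation 0 (exact).**
- Critical values: 2.241 at two-sided 0.025, and 1.960 at 0.05.
- Mean of the test statistic for 80% power at 0.025: 2.241 + 0.842 = 3.083.
- Power of the same test at 0.05: Φ(3.083 − 1.960) = 0.869.
- Holm, per outcome: 0.80 + 0.80·(0.869 − 0.80) = 0.855, against 0.80.
- Both outcomes: split 0.80² = 0.640; Holm 0.640 + 2·0.80·(0.869 − 0.80) = 0.751.

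**3. Other correlations.** The protocol gives no correlation between the two test statistics, so it is an assumption and is ranged. Each row rests on 2 million simulated pairs of normal statistics.

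| Correlation | Per outcome, split → Holm | Both, split → Holm | At least one, either rule |
|---|---|---|---|
| 0 | 80.0% → 85.6% | 64.1% → 75.2% | 96.0% |
| 0.3 | 80.0% → 85.0% | 66.6% → 76.6% | 93.4% |
| 0.5 | 80.0% → 84.6% | 68.7% → 77.9% | 91.3% |
| 0.8 | 80.0% → 83.8% | 72.9% → 80.4% | 87.1% |

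The last column is the same for both rules because Holm's first step is also at 0.025.

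**4. Only one outcome responds.** The second test then helps only when the null outcome is falsely rejected: 0.80 + 0.025·0.069 = 0.802, a gain of about 0.2 points.

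**5. Family-wise error.** With both nulls true it is the same for the two rules: 4.9% at correlation 0, falling to 4.0% at 0.8. With one null true and the other outcome at 80% power, Holm gives 4.5% at correlation 0. With one null true and a very strong effect on the other, it reaches 5.0%. The bound is therefore at most 5%.

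**6. The full sample.**
- f² = 0.15, N = 360: λ = 0.15·360·2/0.7 = 154, and power is about 1.00 under both rules and every noncentrality convention tried.
- Reading 0.15 as f, default convention: λ = 0.0225·360·2/0.7 = 23.1. Power is 99.5% → 99.8% per outcome and 99.0% → 99.6% for both.
- On 360, 80% power at 0.025 corresponds to f² of about 0.0093 (default convention), roughly one sixteenth of the stated 0.15.
- Reading 0.15 as f and also using a less favorable convention leaves power near 0.72 at N = 360. For comparison, at 70.4% power per test and correlation 0, Holm gives 70.4% → 76.7% per outcome and 49.6% → 62.1% for both.

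**The case against.** The strongest reply is that the protocol may contain nothing to correct. The 0.025 is a planning level in the Sample Size section, and the Statistical Analysis section sets no threshold. A Holm plan would also be powered at 0.025, and the SAP, which is not shown, may already specify Holm. That stands as a condition on the fix. It does not remove the point, because the split is the only rule the protocol states for the primary outcomes.

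The second reply is about size, and it stands. The stated 80% belongs to 120 patients per center, whereas the analysis describes one two-group comparison over the whole trial. On 360 patients at the stated effect the gain is 0 to 0.6 points. A reader might infer from the 64-69% and 75-78% figures that the trial is losing about ten points of power. The documents do not support that: the loss needs true effects well below those planned.

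Two other inferences also go too far. The split does not mishandle type 1 error. Nor does the trial require success on both outcomes: Primary Objectives sets no such rule, so power for both bears on the hypothesis but is not a stated success criterion.

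The last reply is timing. All 6-month data were in by January 2025, and Randomization and Blinding says researchers and participants could not be blinded during the intervention. Moving to a more permissive rule late invites questions about pre-specification. This stands too, although the same section says outcome analysis is done by staff blinded to assignment. The change is defensible only if dated before any comparison by arm.

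**Conclusion.** The point holds as one of efficiency, not error. For two unranked primary outcomes, Holm dominates the plain 0.05/2 split: it never loses a rejection and keeps family-wise error at or below 5% under any dependence.

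The size depends on the true power per test. At 80% power for each outcome and an assumed correlation of 0 to 0.5, the gain is about 5 points per outcome and 9 to 11 points for confirming both. It is practically nil at the stated f² on 360 patients, about 0.2 points when only one outcome responds, and zero for winning on at least one. It is worth adopting as inexpensive protection against effects smaller than planned. It gives no reason to doubt a result obtained with the split.

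**What to change.** First check the SAP; if it already specifies Holm, nothing is needed. Otherwise add to the Statistical Analysis section a dated statement, made before any comparison by arm: the two primary outcomes are tested by the Holm procedure at an overall two-sided 5% level, with the smaller p-value tested at 0.025 and, if that is significant, the other at 0.05. If a comparison by arm has already been made, keep the split.

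Leave the sample-size alpha at 0.025, which is also Holm's first step, so no sample-size change follows. The cost is one sentence and a small loss of simplicity: confidence intervals that match Holm exactly are less simple than Bonferroni intervals. The protocol states no interval level for the primary outcomes. If 97.5% intervals are chosen, they may be slightly conservative relative to the second test, and the report should say so.
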